**Fig. 2 Fig2:**
[figure not shown]
Treatment of the phantom head when wearing the MVN Link system by Xsens. Subjects can move freely without interference with the measurement system

**Table 1 Tab1:** Standardized tasks for the fields of specialization: The group of general dentists and the control group of students execute the same tasks. All tasks in the four dental quadrants will be executed on each of the four treatment concepts

	Task	Quadrant 1	Quadrant 2	Quadrant 3	Quadrant 4
**General Dentistry/Students**		**Tooth filling of tooth 16**	**Preparation of tooth 26 for crown uptake**	**Root canal treatment on tooth 35**	**Tartar removal in the 4th quadrant**
	**1**	prepare tooth cavity with a cylindrical diamond bur and the use of wedges	Occlusal reduction using an occlusal reducer	Performing an entrance cavity and trepanation on tooth 35 using a diamond-coated cylinder	Removal of supra- and subgingival tartar/calculus using scalers an curettes
	**2**	Create a Tofflemire die using a die clamp	chamfer preparation using a torpedo-shaped diamond burand approximal reducer	Find the channel entrance using an endo file	
	**3**	Tooth filling with ketac® while using a ketac®-set and a cougar/heidemann		Manual preparation of the canal using an ISO 20-40 endo file with regular irrigation using a irrigation cannula	
**Endodontology**		**Root canal treatment of tooth 16**	**Root canal treatment of tooth 26**	**Root canal treatment of tooth 36**	**Root canal treatment of tooth 46**
	**1**	Application of the rubber dam	Application of the rubber dam	Application of the rubber dam	Application of the rubber dam
	**2**	Trepanation of the tooth and access preparation including the enlarging of the root canal entrance	Trepanation of the tooth and access preparation including the enlarging of the root canal entrance	Trepanation of the tooth and access preparation including the enlarging of the root canal entrance	Trepanation of the tooth and access preparation including the enlarging of the root canal entrance
	**3**	Root canal preparation with hand files at a certain working length, irrigation after each file and remove of the rubber dam	Root canal preparation with hand files at a certain working length, irrigation after each file and remove of the rubber dam	Root canal preparation with hand files at a certain working length, irrigation after each file and remove of the rubber dam	Root canal preparation with hand files at a certain working length, irrigation after each file and remove of the rubber dam
**Orthodontics**		**Multiband Treatment**	**Multiband Treatment**	**Multiband Treatment**	**Multiband Treatment**
	**1**	Acid etching	Acid etching	Acid etching	Acid etching
	**2**	direct bonding of braces on teeth 1, 3, 4 and 6 and opening of self-ligating braces	direct bonding of braces on teeth 1, 3, 4 and 6 and opening of self-ligating braces	direct bonding of braces on teeth 1, 3, 4 and 6 and opening of self-ligating braces	direct bonding of braces on teeth 1, 3, 4 and 6 and opening of self-ligating braces
	**3**	insertion of archwire	Insertion of archwire	Insertion of archwire	Insertion of archwire
	**4**	Integration of brackets 3 using elastic ligation	Integration of brackets 3 using elastic ligation	Integration of brackets 3 using elastic ligation	Integration of brackets 3 using elastic ligation
	**5**	Integration of brackets 1 and 4 using metal ligation	Integration of brackets 1 and 4 using metal ligation	Integration of brackets 1 and 4 using metal ligation	Integration of brackets 1 and 4 using metal ligation
	**6**	Debonding of brackets	Debonding of brackets	Debonding of brackets	Debonding of brackets
**Oral surgery**		**Surgical removal of tooth 13**	**Surgical removal of tooth 23**	**Surgical removal of tooth 38**	**Surgical removal of tooth 48**
	**1**	palatinal and marginal incision in regio 16 to 11.	Vestibular and marginal incision in regio 21 to 25.	Crestal incision in regio 38 with a mesial relieving incision.	Crestal incision in regio 48 to 44.
	**2**	Exposure of the palatinal impacted tooth 13 by osteotomy using a surgical round bur. If necessary, cut through the tooth using a Lindemann bur. Remove the tooth 13 using a Bein root elevator or a dental forceps. Curretage of the dental sac.	Exposure of the vestibular impacted tooth 23 by osteotomy using a surgical round bur. If necessary, cut through the tooth using a Lindemann bur. Removal of the tooth 23 using a Bein root elevator or a dental forceps. Curretage of the dental sac.	Exposure of the impacted tooth 38 by osteotomy using a surgical round bur. Removal of the tooth 38 using a Bein root elevator or a dental forceps. Curretage of the dental sac.	Exposure of the impacted tooth 48 by osteotomy using a surgical round bur. If necessary, cutting through the tooth using a Lindemann bur. Removal of the tooth 48 using a Bein root elevator or a dental forceps. Curretage of the dental sac.
	**3**	Wound closure with single loop interrupted sutures	Wound closure with single loop interrupted sutures.	Wound closure with single loop interrupted sutures.	Wound closure with single loop interrupted sutures.

### Evaluation criteria

The endpoints of the questionnaire are mainly collected through selection options (nominal scales) or ordinal scaled items. In some cases, open answers are also possible.

From the data of the biomechanical analysis, a risk score is determined for every recorded frame using the Rapid Upper Limb Assessment (RULA) [38]. On the basis of this amean score and SD for wrist and arm (Section A) and neck, trunk and leg (Section B) can be determined via RULA [38]. Furthermore, the percentage of time spent in the respective risk scores and at high risk should be determined. Both score values result in an overall score that indicates the level of MSD risk of the examined activity [38].

### Statistical data analysis

Only those questionnaires that have been fully completed will be included in the questionnaire evaluation. The data formatting is done via Excel. The questionnaires are checked for plausibility in the answering behavior. A category system will be developed for open answers. The questionnaire will be evaluated in IBM SPSS Statistics 26, and the questionnaire data will be evaluated descriptively, separately for dentists and dental students, and for dental assistants and trainees. Therefore, measures of location and dispersion corresponding to the scale level are calculated.

The data analysis of the biomechanical measurements is performed with MATLAB® vR2018a software (The Mathworks Inc., Natick, MA, USA). The RULA risk scores will be presented separately for dentists and dental assistants in each of the four treatment concepts for each field of dental specialization.

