## Background

Musculoskeletal disorders (MSD) are common among dental professionals [1–6]. The prevalence of MSD among dentists, dental assistants and dental students varies between 10.8 and 97.9% dependent on the body region according to Lietz et al. [2]. The trunk, neck, shoulders and wrists are the most commonly affected areas [1, 2, 4, 7, 8], often resulting in sick leave or even premature retirement [6, 8–11]. According to Brown et al. [9] a questionnaire survey of early retired dentists from a British insurance company found that MSD are the main cause of ill health retirement at 55%.

In general, the study situation indicates that the causes of MSD are related to the physical demands of the dental profession [3, 12]. The complex and fine-motor activities in the patient’s mouth, which is difficult to inspect, often require the sole attention of the practitioner. Ergonomic posture is therefore neglected in favor of better vision, although initial studies show that an upright trunk posture does not necessarily reduce the quality of treatment [13]. Posture is often static in awkward postures, especially in the trunk, neck and head, while treatment techniques require many, short and repetitive movements of the arms and hands [1, 3].

In addition to the narrow patient’s mouth, the arrangement of the dental workplace (patient chair, equipment and cabinets) also influences the posture and movement of the dental professionals. In the arrangement of the components, a distinction is made between four different treatment concepts [14–16] (Fig. 1). In all four concepts it is planned that the dentist performs treatment together with an assistant. Accordingly, both must have (ergonomically) appropriate access to the necessary equipment and materials and be able to inspect and to work in the patient’s mouth. Although MSD have already been the subject of much research in dentistry, a distinction between the various basic concepts and between the various specializations has not yet been considered.

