## Methods

### Subjects

#### Online survey

For the Germany-wide online survey, a total of at least 1000 completed questionnaires are targeted in the return. The target group includes dentists and dental assistants as well as dental students and dental assistant trainees.

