### Recruitment

The distribution of the questionnaire link as well as the search for participants for the biomechanical measurements will be carried out via the different German dental associations. In order to reach the highest possible number of practicing dentists and dental assistants for the questionnaire, the acquisition of study participants will be done through the state dental associations of all German federal states. In addition, a flyer for the survey is to be created, which will be distributed at various dental meetings. In order to include a high number of dental students, all medical university clinics in Germany will be contacted.

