A further advantage of the RULA is that both the statically held positions of the trunk and the proximal upper extremities are taken into account, as well as the repetitive movements of the hands, which also poses a risk for MSD [39, 41]. Questionnaire surveys in dental professionals have already shown in the past that wrists and hands are also affected by MSD [1, 39]. In addition to the movements, the vibration of the devices also contributes to this [42]. In Germany, only carpal tunnel syndrome is acknowledged as a musculoskeletal occupational disease in dentistry [43].

Although the body of literature is already relatively large with regard to ergonomic risk in dentists, a comparison of the different treatment concepts is still missing. Thus, it has not yet been considered whether the arrangement of the inventory and the positioning of dentist and assistant in relation to the patient have an influence on posture and movement sequences. If differences occur here, this information can be integrated into the development of preventive measures.

The aim should be that both practitioners complement each other in their grasping movements to the instruments and in their work in the patient’s mouth. This should reduce the physical strain on both. The presented study design with the standardization of the tasks performed on a dummy head allows comparisons between the treatment concepts for the first time.

Furthermore, the comparison of the specialization fields with the control group can be expected to contribute to the clarification of the question at which stage of the work experience unfavorable postures occur. Finsen et al. [3] for example, were able to show by means of a questionnaire survey that the prevalence of MSD increases with increasing years of work experience.

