### Limitations

The questionnaires will be distributed through a non-probabilistic procedure and the people contacted can decide to participate self-selectively. Therefore, a distortion is possible, as especially persons who are interested in ergonomic topics in dentistry could be motivated to participate. The representativeness of the results could be affected.

Since the measurements are carried out in laboratory settings, it is possible that no realistic measurement conditions are available. The recordings are not made in the dentists own practice, so that routine work processes may not be correctly recorded. In addition, a dummy head is used to improve the standardization of work processes. The movement frame of the dummy head is based on physiological conditions. The risk of setting unrealistic head positions on the dummy is therefore low. However, under real conditions, it should be noted that the mobility of the cervical spine varies in patients.

No conclusions can be drawn on the dose-response relationship between posture and MSD on the basis of this study. If, however, it is known which basic concepts and working methods are fundamentally in favor of unergonomic working methods, follow-up studies in this field can specifically determine the duration and frequency of treatments in practice.

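### The survey analysis groups dentists with students and assistants with trainees, so a pooled prevalence would move with the share of respondents still in training; the four groups should be reported separately

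*Protocol article*

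**What the plan says.** All references are to the protocol article.

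- **Reporting groups (Statistical data analysis).** The questionnaire is to be "evaluated descriptively, separately for dentists and dental students, and for dental assistants and trainees", using measures of location and dispersion suited to the scale of each item.
- **Who is surveyed (Subjects, Online survey).** "The target group includes dentists and dental assistants as well as dental students and dental assistant trainees". Four groups are named one by one.
- **Size (same section).** "a total of at least 1000 completed questionnaires are targeted in the return". The figure is a total, with no split by group.
- **Recruitment.** State dental associations are approached "In order to reach the highest possible number of practicing dentists and dental assistants for the questionnaire". Students have a channel of their own: "In order to include a high number of dental students, all medical university clinics in Germany will be contacted". No separate channel is described for trainees.
- **Sampling (Limitations).** "The questionnaires will be distributed through a non-probabilistic procedure and the people contacted can decide to participate self-selectively". The section warns of over-representation of people interested in ergonomics; it does not discuss the mix of qualified and training respondents.
- **Expected difference (Discussion).** An earlier questionnaire study is cited as showing that "the prevalence of MSD increases with increasing years of work experience".
- **Aim (Discussion and Conclusion).** The survey is meant to give the prevalence of MSD in dental professionals. In the movement analysis, by contrast, students and trainees form a distinct control group (Aims; Subjects, Biomechanical analysis).

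**The concern.** If each stratum yields one prevalence, that figure is a weighted average of two prevalences that the article itself leads the reader to expect to be unequal. The weights are not those of any stated population. They follow from how well two recruitment channels work and who chooses to answer. Two equally well-run rounds of this survey could report different prevalences for the same body region only because one drew more students.

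The pull would be towards the less exposed group, so the figure would tend to understate prevalence in practising dentists and assistants. Lifetime prevalence, one of the planned recall periods, accumulates with time and may be the most affected. A larger sample does not help, since the shift does not depend on n.

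Pooling would also hide something the survey could show. The Background calls it unclear whether unfavourable movement patterns appear only with years of work or already during training, and the contrast between those in training and those in practice bears on that question.

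**Working it through.** **Step 1: what the sentence fixes.** The comma and the repeated preposition split the sentence into two units: dentists with students, and assistants with trainees. A four-way split would more naturally be a plain list, as in the description of the target group. The two-stratum reading is the more natural one, though not the only one.

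**Step 2: inputs.**
- Total target: at least 1000 (Subjects, Online survey). No precision, prevalence or other basis is given, so there is nothing to reproduce, and the point does not turn on it.
- Direction of the difference: higher prevalence with more years of work (Discussion). No size is given.
- Published prevalence: 10.8% to 97.9% by body region (Background), for dentists, assistants and students together. It does not yield a difference between groups.
- Assumed: prevalence of 70% in the qualified group; a difference d of 0, 10, 20 or 30 points; a share w in training of 10%, 30% or 50%.

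**Step 3: formula.** With p_q the prevalence in the qualified group and p_t that in the group in training,

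pooled = (1 − w) × p_q + w × p_t = p_q − w × d, where d = p_q − p_t.

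The shift away from p_q is w × d. It does not depend on the assumed 70%.

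**Step 4: results (pooled prevalence, p_q = 70%).**

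| Difference d | w = 10% | w = 30% | w = 50% |
|---|---|---|---|
| 0 points | 70% | 70% | 70% |
| 10 points | 69% | 67% | 65% |
| 20 points | 68% | 64% | 60% |
| 30 points | 67% | 61% | 55% |

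At a 30% share, a difference of 10 points shifts the figure by 0.30 × 10 = 3 points, and one of 20 points by 0.30 × 20 = 6 points.

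**Step 5: comparison with sampling error.** The nominal 95% half-width at p = 50% is 1.96 × √(0.25/n):

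- n = 500 (one of two equal strata, assumed): 1.96 × √(0.25/500) = 4.4 points
- n = 250 (one of four equal groups, assumed): 1.96 × √(0.25/250) = 6.2 points

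In a stratum of 500, the change in share that moves the estimate by one half-width is 4.38/d: about 22 percentage points if d is 20 (4.38/20 = 0.219), and about 44 if d is 10 (4.38/10 = 0.438). The effect is thus comparable with sampling error if the difference is sizeable and the share uncertain, and small otherwise.

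**Step 6: after the change.** Reported by group, each prevalence is p_q or p_t alone, and w drops out.

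**The case against.** The strongest reply is that the sentence never says one prevalence will be calculated for dentists plus students. It could mean two reports by professional line, each with its own subgroups, or four groups. The separate control group in the movement analysis shows that the authors distinguish the two levels of training. This stands as a possibility: under that reading the problem disappears. But it is the less natural reading, and the sentence would still need rewording to say so.

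Second, a reader might infer that the survey has no quotas or weights at all. The documents do not support this. The article condenses a fuller plan, and its silence proves nothing. The point needs only what is stated: the grouping, a target given as a total, and self-selected participation.

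Third, recruitment also seeks as many practising dentists and assistants as possible, so a large student share is not a foregone conclusion. This is correct. For trainees, moreover, no separate channel is described, so the recruitment argument bears mainly on the dentist and student stratum. In the other stratum the share is still set by who responds.

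Fourth, the size is assumed. This also stands: the documents give a direction only, and for years of work rather than for students against dentists as such.

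Three stronger readings are tempting and should not be made:
- **That the grouping neglects specialisation.** The Background remark that "a distinction between the various basic concepts and between the various specializations has not yet been considered" describes earlier research. The article assigns that comparison to the movement analysis, which does report by field, and specialisation is not listed among the survey items.
- **That the results could not be compared with other surveys.** Comparison is harder if the mix is unknown, but not ruled out; the literature the article cites covers students too.
- **That the figures must be standardised to a professional register.** This needs data outside the documents and would not cure the self-selection that Limitations already admits.

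**Conclusion.** The point holds as a weakness in a stated analysis choice. On its natural reading, the sentence pools groups that the article's own evidence suggests differ, in proportions that no stated population determines, while the aim is prevalence in dental professionals. The general self-selection caveat does not cover this. Unlike self-selection, it can be removed at the analysis stage.

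The size cannot be established from the documents. On the illustrative assumptions, the shift is 3 to 6 points at a 30% student share, and zero if the groups do not differ. The conclusion rests on two things: that the two-stratum reading is the intended one, and that the reported rise in prevalence with years of work carries over to the contrast between people in training and qualified staff. It affects how a main survey output is interpreted; it does not touch the movement analysis.

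**What to change.** Reword the sentence in Statistical data analysis so that dentists, dental students, dental assistants and dental assistant trainees are evaluated as four separate groups, each shown with its number of respondents. State that the prevalence in dental professionals is based on the two qualified groups. If a figure pooled over qualified and training respondents is still wanted, label it secondary and give the mix beside it. If four groups were always intended, the same rewording settles the ambiguity.

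No new data should be needed: the planned split already requires each respondent's professional line, and the target group is defined by the four categories. The work is extra table columns. The cost is precision per group: with an assumed even split of 1000, a half-width of about 6.2 points at 250 against 4.4 at 500, and wider still in any group that responds poorly. These intervals are nominal, because the sample is not random.

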## Discussion

The aim of this study, is to assess the prevalence of MSD in dental professionals for all relevant regions of the body. In addition, a kinematic movement analysis will be used to record typical dental work procedures on all four treatment concepts. With the use of the RULA, the postures recorded will be examined with regard to their ergonomic risk. On the basis of these investigations, a comprehensive knowledge gain regarding work-related MSD in dentistry and their possible biomechanical causes is possible. Such an approach has not yet been published.

The current evidence in the field of task and movement analyses indicates that dental work is largely characterized by unfavorable static postures of the neck, back and shoulders [20, 29, 39]. Such postures are not only in dentistry, but also generally among the risk factors for occupational MSD [40]. To maintain these static postures, a permanent isometric contraction of > 50% of the body’s muscles is necessary [39]. This can lead to changes in blood flow, contractile activity and, in the long term, morphology and nociception [20]. A kinematic 3D analysis of dental activity by Finsen et al. [3] from 1999 (recordings from two video cameras) shows that a neck flexion of > 30° was held for 82% of working time. An arm abduction > 30° was recorded for 36% of the working time. In order to obtain even more detailed movement analyses of the whole body during dental work, the newly developed inertial sensors used here are preferable, as the practitioners are positioned close to the patient’s chair and with their legs even below it. The legs of dentist and assistant are often interlocked and the patient chair blocks the cranial view on the legs. When data is collected using optical motion capture, the field of view of the cameras could therefore be impaired, making it difficult to take pictures of the entire body.

The ergonomic evaluation of the inertially collected data using the RULA allows a detailed ergonomic risk assessment of the work processes. While observational methods are traditionally filled in manually and therefore can only provide a rather subjective snapshot, the approach presented allows an objective risk assessment for each frame captured. The continuous data therefore contribute to the breakdown and ergonomic evaluation of smallest work sections [34, 36]. On the basis of this, a better understanding of MSD risks in dentistry can be contributed.

A further advantage of the RULA is that both the statically held positions of the trunk and the proximal upper extremities are taken into account, as well as the repetitive movements of the hands, which also poses a risk for MSD [39, 41]. Questionnaire surveys in dental professionals have already shown in the past that wrists and hands are also affected by MSD [1, 39]. In addition to the movements, the vibration of the devices also contributes to this [42]. In Germany, only carpal tunnel syndrome is acknowledged as a musculoskeletal occupational disease in dentistry [43].

Although the body of literature is already relatively large with regard to ergonomic risk in dentists, a comparison of the different treatment concepts is still missing. Thus, it has not yet been considered whether the arrangement of the inventory and the positioning of dentist and assistant in relation to the patient have an influence on posture and movement sequences. If differences occur here, this information can be integrated into the development of preventive measures.

The aim should be that both practitioners complement each other in their grasping movements to the instruments and in their work in the patient’s mouth. This should reduce the physical strain on both. The presented study design with the standardization of the tasks performed on a dummy head allows comparisons between the treatment concepts for the first time.

Furthermore, the comparison of the specialization fields with the control group can be expected to contribute to the clarification of the question at which stage of the work experience unfavorable postures occur. Finsen et al. [3] for example, were able to show by means of a questionnaire survey that the prevalence of MSD increases with increasing years of work experience.

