**Methods:**

To evaluate the prevalence of MSD in dental professionals, 1000 responses will be collected from a nationwide (Germany) online questionnaire (mod. Nordic Questionnaire and mod. Meyer questionnaire). In order to assess the ergonomic risk of the treatment techniques used in the four treatment concepts, 3D movement analyses are carried out with inertial sensors. For this purpose, 20 teams of dentists and dental assistants from four dental fields of specializations (generalists, orthodontists, endodontists and oral surgeons) and a student control group will be recruited. Each team will execute field specific standardized treatments at a dummy head. Measurements are carried out in each of the four treatment concepts. The data will be analyzed using the Rapid Upper Limb Assessment (RULA) which will be modified for the evaluation of objective data.

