### Aims

The aim of this study is to comprehensively investigate MSD in the dental professional field. Initially, a Germany-wide online questionnaire will be used to collect data on MSD, work flow and health-related activities among dental professionals. Furthermore, an ergonomic risk assessment of the cooperative treatment of dentists and dental assistants based on objective movement data will be carried out for the first time. This will be done for four specializations (generalists, oral surgeons, endodontists and orthodontists) and a control group of dental students and dental assistant trainees at each of the four treatment concepts. The activities will be carried out in a standardized manner on the dummy head, so that differences between the treatment concepts can be recognized.

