#### Motion capturing

The recording of the posture in the different test situations will be carried out by means of the inertial motion capture system MVN Link from XSens (Enschede, Netherlands). Sampling rate is 240 Hz and the measurement error is specified by the manufacturer as ±1%. By means of 17 sensors 22 joints will be interpolated.

After the measuring suit has been put on, the recordings take place over a period of 1 h on each of the four treatment concepts (4 h in total): On a dummy head, which is attached to each of the four treatment concepts, dental activities per specialization are carried in a standardized sequence (Fig. 2). The activities within each specialization are performed in all four quadrants (Table 1 for treatments of the respective fields of dental specialization). In addition to the individual biomechanical analysis, the interaction between dentist and dental assistant is recorded synchronously. In order to be able to allocate the activities exactly, the entire measurement sequence is filmed simultaneously in a total view (iPad Air, Apple Inc., Cupertino, California, United States; resolution: 1080p HD, 120fps). Therefore, measurement system and the camera will be synchronized by means of the software. Due to the character of the work, no randomization of the tasks will be carried out.

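### Students perform only the general-dentistry tasks, so comparing them with the other three fields mixes procedure with work experience

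*Protocol article*

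**What the plan says.** The Background asks whether unfavourable movement patterns develop over years of practice or are already present in students and trainees. The Discussion returns to this and says that "the comparison of the specialization fields with the control group can be expected to contribute to the clarification of the question at which stage" of a career such postures appear. Fields are in the plural, and nothing restricts the statement to one of them. The Aims count generalists, oral surgeons, endodontists and orthodontists as the four specialisations, and add "a control group of dental students and dental assistant trainees at each of the four treatment concepts".

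Tasks are assigned by field. The Abstract states: "Each team will execute field specific standardized treatments at a dummy head". The section Motion capturing says that "dental activities per specialization are carried in a standardized sequence". The caption of Table 1 places the control group: "The group of general dentists and the control group of students execute the same tasks". The other three fields have their own task sets.

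The section Statistical data analysis presents the RULA scores separately by role, treatment concept and field. It states neither a task-matched nor a task-adjusted comparison with the control group. The Limitations cover self-selection, the laboratory setting, the dummy head and the lack of dose-response information. They do not cover the task difference between students and three of the four fields.

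**The concern.** For a comparison of professionals with students to inform a question about experience, the two groups should be doing the same work. In three of the four fields they are not. The Background says that different treatments might affect posture, and it cites a direct comparison in which generalists had less favourable postures than orthodontists. Both of those groups were practising professionals, so the article already reports a difference between fields.

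If that difference carries over to the standardised tasks, students doing general-dentistry work could score worse than orthodontists with no effect of experience at all. A real worsening with experience could be masked or reversed. At stake is a secondary conclusion about when poor postures are acquired, which the article links to its open question on students and trainees.

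**Working it through.** The plan gives no figure on this point to reproduce, and no sample size, power or alpha bears on it. The check concerns the structure of the design.

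**Step 1. Task sets, from Table 1.**

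| Quadrant | General dentists and students | Endodontists | Orthodontists | Oral surgeons |
|---|---|---|---|---|
| 1 | Filling, tooth 16 | Root canal, tooth 16 | Multiband | Removal, tooth 13 |
| 2 | Crown preparation, tooth 26 | Root canal, tooth 26 | Multiband | Removal, tooth 23 |
| 3 | Root canal, tooth 35 | Root canal, tooth 36 | Multiband | Removal, tooth 38 |
| 4 | Tartar removal | Root canal, tooth 46 | Multiband | Removal, tooth 48 |

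Orthodontic steps (for example "direct bonding of braces on teeth 1, 3, 4 and 6 and opening of self-ligating braces") and surgical steps (for example "palatinal and marginal incision in regio 16 to 11") have no counterpart in the student set. Endodontists and students overlap in procedure type in quadrant 3 only. Even there the tooth differs (36 versus 35), and "Application of the rubber dam" is listed for endodontists but not for students.

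**Step 2. What each comparison estimates.** Take the simplest model: group mean = task effect + experience effect. Let G, N, O and S be the whole-session task effects of general dentistry, endodontology, orthodontics and oral surgery, and let E be the effect of being experienced. Students have mean G.

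- General dentists minus students = (G + E) − G = E
- Endodontists minus students = (N + E) − G = E + (N − G)
- Orthodontists minus students = (O + E) − G = E + (O − G)
- Oral surgeons minus students = (S + E) − G = E + (S − G)

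Only the first isolates E. Solving the five group means for E gives weights of +1 for general dentists, −1 for students and 0 for each of the other three fields. In this model those three fields add nothing to the estimate of experience through a comparison with students.

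**Step 3. Pooling does not help.** The mean of the four fields minus students is (G + N + O + S)/4 + E − G = E − 0.75G + 0.25N + 0.25O + 0.25S. The task terms vanish only if the average of N, O and S equals G, which nothing in the article supports.

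**Step 4. Size.** The section on subjects for the biomechanical analysis plans 20 teams in each of four fields and 20 in the control group. That is 4 × 20 = 80 professional teams. The task-matched comparison uses 20 of them against 20 control teams. The other three fields hold 3 × 20 = 60 teams, or 60/80 = 75%. This share describes how widely the Discussion sentence reaches beyond the matched pair. It is not a count of planned tests.

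**Step 5. What the matched pair can show.** General dentists versus students has two levels, professional and trainee. It can show whether the two differ on the same task. It cannot by itself say at which point in between a difference arises.

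**The case against.** The strongest reply is that this is a mildly worded sentence in a Discussion. It says only that the comparison may help to clarify the question. The Aims tie standardisation to differences between treatment concepts and state no experience comparison, and the analysis section is descriptive. A reader might infer that four formal field-versus-control contrasts are planned, or that the experience question is to be settled by them. The article supports neither reading. This part of the reply stands and lowers the weight of the point.

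Second, the design already contains the valid comparison, and the Table 1 caption makes the matching visible. The students' own scores also bear on whether trainees already show unfavourable patterns, with no cross-field contrast needed. Both are true, but the Discussion sentence is not limited to that comparison.

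Third, a reader might infer that endodontists do entirely different work from students. Table 1 does not support that. RULA is scored on every frame, and synchronised video allows activities to be allocated, so a comparison limited to quadrant 3 is feasible. It would be only roughly matched, and whole-session scores would remain mixed.

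Fourth, a condensed article may leave the specification of contrasts to a fuller document. That explains missing detail. It does not change the task allocation, and no analysis of the student comparison can recover an experience effect for procedures that students never perform without assuming something about the task effects.

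**Conclusion.** The concern holds as a secondary point of interpretation. As worded, the Discussion invites an experience reading of comparisons that mix task with experience. This is complete for orthodontists and oral surgeons. For endodontists it holds at whole-session level, with one roughly similar procedure in common. Only general dentists versus students, 20 teams against 20, is task-matched, and even that two-level contrast cannot locate the stage at which postures change.

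The algebra assumes additive task and experience effects, and that experience is the only systematic difference within the matched pair. If experience acts differently by procedure, the other three comparisons are no easier to interpret. The size and direction of any bias are unknown, because the article gives no RULA values by task.

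A reader might go further and conclude that the study's main comparison is compromised. It is not. Each team works at all four treatment concepts with its own tasks held fixed, so the within-team comparison of concepts is untouched. The point calls for correction of the text and of the planned interpretation. It does not call for a change of design.

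**What to change.** 1. In the Discussion, and wherever the comparison is specified, restrict the experience inference to general dentists versus students and the general dentists' assistants versus trainees, within the same task, quadrant and treatment concept.
2. In the Limitations, state that differences between endodontists, orthodontists or oral surgeons and the control group cannot be attributed to experience, because the tasks differ. If the quadrant 3 root canal comparison with endodontists is shown, label it as only roughly matched.
3. State there too that a two-level contrast cannot by itself show at which stage unfavourable postures arise.
4. Optionally, explore within each field the association between RULA score and years in the profession, where the task set is constant. This is possible only if the questionnaire completed before the measurements records that item. The article mentions sociodemographic data and working habits but does not name years in the profession.

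Items 1 to 3 need wording only, with no new data, teams or measurements. The price is a narrower secondary claim.
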